### Sample size considerations

The primary analysis will compute the proportion of subjects with a 4-fold decrease (from study entry RPR) in RPR titers from baseline by six months in the per-protocol (PP) analysis population.

We have powered this study to detect a significant difference from a minimal accepted efficacy of standard treatment with benzathine penicillin (80%). This minimal efficacy was selected based on a multi-center clinical trial evaluating the efficacy of penicillin versus azithromycin [36].

A 90% response rate for cefixime was selected based on recent meta-analyses, a multi-center trial of ceftriaxone for treatment of syphilis [10, 11, 37, 38]. To calculate the number of subjects required to enroll to reach 94 evaluable subjects in the PP analysis population, the following assumptions are made:

Using a two-sided exact binomial test at α = 5%, a sample size of 107 achieves an 80% power to detect a minimum acceptable cefixime efficacy (p_0_) of 0.80, assuming the anticipated efficacy proportion (p) of 0.90. Assuming 20% dropout rate and other related factors, the final sample size for the cefixime arm is inflated to *N* = 140, with correspondingly 70 participants recruited in the BPG arm, in a ratio (cefixime to BPG) of 2:1 (Table 4).

**Table 4 Tab4:** Sample size to detect a minimum acceptable efficacy (p_0_) of 0.80 using a two-sided Exact binomial test for difference assuming alpha = 5% and power = 80%*

Anticipated efficacy *P*	Sample size *	Effective sample size (20% inflated) *n*
0.86	316	395
0.87	225	282
0.88	173	217
0.89	131	164
0.90	107	**134**
0.91	88	110
0.92	69	87
0.93	55	69
0.94	48	60
0.95	41	52
0.96	34	43
0.97	26	33
0.98	26	33
0.99	17	22

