### Study outcomes evaluation

#### Primary analysis

The primary outcome is the proportion cured using cefixime treatment, evaluated at six months post-recruitment.

Proportion representing proportion cured using cefixime treatment success, cure defined as at least 4-fold reduction in RPR titer by six months (compared to baseline). Participants experience a 4-fold reduction in RPR before six months will be counted as a success at six months.

The primary analysis will assess whether the proportion cured is greater than or equal to 90% and whether the observed efficacy is statistically different than the minimally acceptable efficacy set at 80%. Proportion cured and 95% confidence intervals will be calculated using the binomial exact test. Cefixime will be declared efficacious if the lower limit for a two-sided 95% confidence interval (CI)≥ 0.80.
*Cure:* At least a 4-fold decrease in RPR from baseline to 6 months.*Failure:* Less than a 4-fold decrease in RPR titer from baseline to 6 months, or an increase in RPR titer.*Non-evaluable:* At least one of the following: Subject did not return for 6 month visit, or RPR results from the 6 month visit were not available for any reason, or subject could not be evaluated for any other reason.

For the PP analysis population, subjects with non-evaluable outcome status will be excluded from the analysis. For the ITT analysis population, subjects with non-evaluable outcome status will be included in analyses and classified as treatment failures. Subjects who discontinued early from the study due to a lack of treatment effect are included in all analysis populations as treatment failures.

The primary efficacy analysis will be based on the cure rate by 6 months and will be performed in the PP analysis population. The primary analysis will also be performed in the ITT population, but this is a secondary outcome measure.

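### The ITT rule counts every woman without a month-6 RPR as a failure against an unchanged 0.80 bar, so ITT mainly measures missingness; it also conflicts with the early-success rule

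*Protocol article*

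**What the plan says.** The Primary analysis section sets one success criterion: "Cefixime will be declared efficacious if the lower limit for a two-sided 95% confidence interval (CI)≥ 0.80". The interval is exact: "Proportion cured and 95% confidence intervals will be calculated using the binomial exact test". Efficacy is decided in the per-protocol (PP) population. The same analysis is then repeated in the intent-to-treat (ITT) population as a secondary outcome measure, with no separate criterion. ITT is defined under Analysis populations as all enrolled subjects.

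A woman is non-evaluable if she misses the 6-month visit, has no 6-month RPR result, or cannot be evaluated for another reason. PP drops such women. In ITT, "subjects with non-evaluable outcome status will be included in analyses and classified as treatment failures".

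The same section also states: "Participants experience a 4-fold reduction in RPR before six months will be counted as a success at six months".

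Sample size considerations plans for loss: "Assuming 20% dropout rate and other related factors, the final sample size for the cefixime arm is inflated to" 140.

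**The concern.** PP removes women who did not comply with treatment and women without a month-6 RPR. ITT is the only other efficacy population described, so a reader will turn to it to see whether those exclusions flattered the result. It differs from PP in two ways at once: it restores the non-compliant women, and it imposes failure on everyone with a missing outcome. If the second effect dominates at realistic loss, a disagreement between ITT and PP says nothing about exclusion bias.

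The two sentences on early response and on non-evaluability also give opposite answers for one identifiable group: women with a documented four-fold fall at month 3 and no month-6 RPR. Under one sentence they are successes. Under the other they are ITT failures and PP exclusions. That affects the numerator in ITT, and both the numerator and the denominator in PP.

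**Working it through.** **Inputs.** Bar 0.80 and anticipated cure rate 0.90 (Sample size considerations; Primary analysis). Exact (Clopper-Pearson) two-sided 95% interval (Primary analysis). Cefixime arm n = 140 (Randomization). Planning allowance 20% (Sample size considerations).

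**The plan's own figure.** The plan says that "a sample size of 107 achieves an 80% power". With p0 = 0.80 and an upper tail of at most 0.025, the critical value at n = 107 is 94 cures. The exact tail is 0.0233 and power at 0.90 is 81.9%. No smaller n reaches 80%, so 107 is reproduced. Inflation: 107 / (1 − 0.20) = 133.75, rounded up to 134, as in Table 4. The arm is then set at 140.

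**Successes needed in ITT.** With denominator 140:

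- 121/140: lower limit 0.796, bar missed
- 122/140 = 87.1%: lower limit 0.804, bar met

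So at most 140 − 122 = 18 women (18/140 = 12.9%) may be non-successes for any reason. If more than 18 are non-evaluable and all count as failures, the bar cannot be met even if every evaluable woman is cured.

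**At the full allowance.** 0.20 × 140 = 28 missing, 112 evaluable.

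- All 112 cured: 112/140 = 80.0%, 95% CI 72.4% to 86.3%
- 90% cured: 0.90 × 112 = 100.8, about 101/140 = 72.1%, 95% CI 63.9% to 79.4%

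**Across a range of missingness.** Let m be the number non-evaluable and X ~ Binomial(140 − m, 0.90). The bar is met if X ≥ 122. The upper limit falls below 0.80 if X ≤ 101.

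| m | Share of 140 | P(bar met) | P(upper limit < 0.80) |
|---|---|---|---|
| 0 | 0% | 89% | negligible |
| 7 | 5% | 31% | negligible |
| 14 | 10% | 0.4% | 0.07% |
| 28 | 20% | 0 | 57% |

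**If the early-success sentence governs instead.** Take m = 28 and suppose k of these women have a documented month-3 response and are credited. The bar is met if X + k ≥ 122, with X ~ Binomial(112, 0.90).

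- k must be at least 122 − 112 = 10 for the bar to be reachable at all.
- With k = 20, 102 of the 112 must be cured, and P(bar met) is about 43%.
- With k = 8, the bar is still out of reach, but P(upper limit < 0.80) falls from 57% to 1.5%.

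The documents give no figure for k. These values are illustrations.

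**The case against.** Missing-as-failure is a common, transparent and conservative rule, and ITT is expressly secondary. Both points stand: the PP decision rule is not touched by the ITT arithmetic. What remains open to criticism is using this as the sole ITT rule, with the 0.80 criterion carried over, alongside a planned loss of this size.

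A reader might infer that the plan itself expects 28 women without a month-6 outcome, so that ITT is bound to fail and an effective drug would more often than not look significantly worse than 80%. The documents do not support this, for three reasons.

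- The 20% is stated together with other related factors, in a calculation aimed at evaluable PP women. PP also excludes non-compliant women, who stay in ITT and are scored on their RPR if they have one. True ITT missingness may therefore be well below 28, and at 14 the 57% becomes 0.07%.
- The zero probability follows only if the non-evaluable sentence overrides the early-success sentence.
- What is missed at 112/140 is the confidence-limit criterion. The point estimate is exactly 80.0%.

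Nor is ITT the only information on exclusions. The plan also tabulates follow-up status by arm, cefixime adherence and rescue treatment, and it keeps early discontinuations for lack of effect as failures in every population. These help to describe the exclusions, but they do not give an all-randomised efficacy estimate.

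Extra sensitivity analyses may be in an analysis plan that is not shown. That would answer part of the point, but it would not remove the conflict between two sentences in the protocol text.

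**Conclusion.** The point holds in this form. Under the literal non-evaluable rule, ITT cannot meet the 0.80 confidence-limit bar once more than 18 of 140 cefixime women (12.9%) lack a month-6 result. At the anticipated 90% cure rate it is already unlikely at 5% missing (31%) and nearly impossible at 10% (0.4%), against 89% with no loss. ITT as written therefore reflects mainly how many women are missing and is a poor check on the PP exclusions.

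These figures assume 140 enrolled on cefixime, a 90% cure rate among evaluable women, and no credit for month-3 responders. The last assumption depends on an unresolved contradiction in the Primary analysis section: with 28 missing, crediting 20 of them moves the chance of meeting the bar from zero to about 43%. The contradiction is a defect in its own right, and it also bears on who enters PP. The fixes below are worth making, but the PP decision criterion need not change.

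**What to change.** 1. Reconcile the two sentences in the Primary analysis section. State which governs a woman with a documented month-3 response and no month-6 RPR, and apply it in both PP and ITT.
2. Add a secondary analysis of all women randomised to cefixime. Every observed month-6 RPR is used regardless of adherence, as the ITT definition already implies. Multiply impute only the month-6 responses still missing after step 1, from baseline, month-3 and month-9 titres and centre. Do not impute protocol-defined failures, or women who received BPG or another anti-syphilis treatment before a documented response. They stay non-successes, so that cefixime is not credited with cures after other treatment.
3. Keep missing-as-failure as a labelled worst-case bound, and say that it is not read against the 0.80 bar.

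Cost: a clarification of the protocol text, analysis-plan wording and modest extra analysis work. No new data are needed, since the titres are already scheduled. The imputation brings in a missing-at-random assumption, which the retained worst case bounds from below.

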### Primary objective

The primary objective of the study is to demonstrate the efficacy, as measured by a 4-fold (or more) decrease in rapid plasma reagin (RPR) titer from baseline to 6 months after treatment, with cefixime 400 mg taken orally two times a day for 10 consecutive days.

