### Analysis populations

#### Per-protocol (PP) population

This analysis population includes enrolled subjects who met all inclusion/exclusion criteria, complied with study treatment, and had RPR test results at the 6-month visit. To be compliant with study treatment, a subject must be able to swallow the pills and not vomit within 30 minutes of administration. No more than two consecutive missed doses will be considered as compliant with study treatment. Completion of at least 7 days of treatment or at least 14 capsules of 400 mg of cefixime will be considered as study compliant.

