### Ethical concerns

#### Potential risks

Potential risks to study participants include the possibility that the alternative treatment may not prove to be effective. For this reason, we will closely follow the subjects for adherence to study medication including daily phone or in-person contact to establish adherence to study drug. RPR titers will be collected 12 weeks after completion of treatment (with no more than 5-day result turnaround time). If the participant experiences an RPR titer increase of 4- fold or more from the entry RPR at 3 or 6 months, we will consider this a treatment failure and the participant and be given 2.4 million units of BPG immediately and according to national guidelines.Risks to privacy: Participants’ attendance at study visits may be accidentally noticed by others.Psychological risks: Receiving a positive syphilis diagnosis could be upsetting to a participant. However, syphilis diagnosis occurs as part of standard clinical care and outside of the study.*Risks associated with blood draw*: Participants may experience discomfort, bruising, or even fainting in connection with the blood draw that will be performed during the visits. There is also a slight risk of infection.Cefixime is contraindicated in patients with known allergy to cefixime or other cephalosporins. Some participants may not be aware of their allergy status. However, anaphylactic or anaphylactoid reactions (including shock and fatalities) have rarely been reported with the use of cefixime, thus this risk is considered to be very low.Some adverse reactions were documented in other cefixime clinical trials. In United States (U.S.) trials of the tablet formulation of cefixime, the most commonly seen adverse reactions were gastrointestinal events. These events were reported among 30% of adult patients that received either the twice daily or the once daily regimen. Discontinuation of cefixime during the U.S. clinical trials occurred among 5% of study participants because of drug-related adverse reactions. Other individual adverse reactions reported from U.S. clinical trials included diarrhea (16%), nausea (7%), loose or frequent stools (6%), flatulence (4%), abdominal pain (3%), and dyspepsia (3%). Observed and reported adverse reactions for cephalosporins including but not limited to cefixime have included allergic reactions, superinfection, renal dysfunction, toxic nephropathy, hepatic dysfunction including cholestasis, aplastic anemia, hemolytic anemia, hemorrhage, and colitis.In this study, participants will be observed for 30 minutes in the clinic following the first dose of cefixime. In the event of an adverse event or an allergic reaction possibly related to cefixime, participants will be evaluated by a study nurse and by a clinic-based study physician. Participants will be referred to emergency services at the discretion of the clinic-based study physician. Cefixime will be discontinued in the event of an allergic reaction.The efficacy of cefixime to prevent mother-to-child transmission of syphilis is unknown. Study participants will be counseled regarding the risk of untreated syphilis in pregnancy. Each participant will be offered oral contraceptive tablets as well as condoms to prevent pregnancy for the duration of the study. Condoms will be provided to each participant and use will be encouraged at each visit to reduce the risk of re-infection with syphilis and infection with other STIs.

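### Efficacy is decided on a per-protocol set that drops women who stop cefixime early for drug reactions, which favours cefixime if those women are cured less often than the rest

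*Protocol article*

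**What the plan says.** **Deciding set.** Under Primary analysis: "The primary efficacy analysis will be based on the cure rate by 6 months and will be performed in the PP analysis population". The same section declares cefixime efficacious when the lower limit of the exact two-sided 95% interval is at least 0.80. Of the ITT repeat it says: "The primary analysis will also be performed in the ITT population, but this is a secondary outcome measure".

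**Who is in PP.** Under Per-protocol (PP) population, women must be eligible and must have "complied with study treatment, and had RPR test results at the 6-month visit". Compliance is spelled out: "To be compliant with study treatment, a subject must be able to swallow the pills and not vomit within 30 minutes of administration". Missing more than two doses in a row breaks compliance. On the amount taken, the section says: "Completion of at least 7 days of treatment or at least 14 capsules of 400 mg of cefixime will be considered as study compliant". The full course is 20 capsules. The Secondary analysis section uses the same 7-day or 14-dose threshold to define tolerability.

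**What happens to early stoppers.** Primary analysis keeps women who discontinue for lack of effect as failures in all sets. No matching rule covers women who stop for intolerance. Those with related toxicity of grade 3 or above stop cefixime, receive benzathine penicillin (BPG) and are removed from the study (Secondary outcome measure; Discontinuation of study enrolment).

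**Expected frequency.** Under Potential risks: "Discontinuation of cefixime during the U.S. clinical trials occurred among 5% of study participants because of drug-related adverse reactions".

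**The bar.** Sample size considerations sets 80% as the minimal accepted efficacy of standard BPG treatment and assumes 90% for cefixime.

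**The concern.** PP membership depends on an event after randomisation that the drug itself can cause. A woman who stops at, say, 8 capsules because of a drug reaction counts against cefixime in the tolerability result but disappears from the efficacy result. Nothing in the plan stops her month-6 RPR from being taken if her reaction was mild or moderate.

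The success criterion works in one direction only: cefixime must clear a fixed 80%. Removing women who did worse makes it easier to clear. Cefixime could then be declared efficacious, and that result could inform a trial in pregnant women, when the cure rate in all women given it is only 80%.

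The ITT repeat does not guard against this. It has no decision attached, and it counts every non-evaluable woman as a failure. With the planned 20% dropout and 0.90 cured among the rest, ITT would show about 0.80 × 0.90 = 0.72 even if all went as designed. A low ITT figure could therefore be put down to missed visits and would not isolate intolerance.

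**Working it through.** **Inputs.** From Sample size considerations and Primary analysis: p0 = 0.80, p1 = 0.90, n = 107, two-sided exact test at 5%, success if the exact lower limit is at least 0.80. From Potential risks: 5% discontinued for drug-related reactions. Assumptions made here:
- d, the share of treated women who leave PP for intolerance. 5% is the document's figure, taken to occur before 14 doses; 2.5% is a lower variant.
- c, the cure rate on cefixime among those women. The documents give no value, so a range is shown.
- Other exclusions from PP are unrelated to outcome.

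**1. The plan's own figure.** At n = 107 the smallest number of cures with a lower limit of at least 0.80 is 94 (93 cures give 0.790, 94 give 0.801). P(X ≥ 94) is 0.023 at p = 0.80 and 0.819 at p = 0.90. The stated n is reproduced, and 107/0.80 = 134 matches Table 4.

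**2. Effect on the estimate.** All-treated rate = (1 − d) × PP rate + d × c. With a PP rate of 0.90 and d = 5%:
- c = 0: 0.95 × 0.90 = 0.855, so PP is 4.5 points higher.
- c = 0.5: 0.855 + 0.025 = 0.88, so PP is 2 points higher.

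**3. Effect on the decision.** Set the all-treated rate to 0.80. Then PP rate = (0.80 − d × c)/(1 − d), and the chance of declaring efficacy is P(X ≥ 94) at that rate with n = 107.

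| d | c | PP rate | P(declare) |
|---|---|---|---|
| 5% | 0 | 0.80/0.95 = 0.842 | 18.5% |
| 5% | 0.4 | 0.78/0.95 = 0.821 | 7.2% |
| 5% | 0.5 | 0.775/0.95 = 0.816 | 5.5% |
| 5% | 0.8 | 0.76/0.95 = 0.800 | 2.3% |
| 2.5% | 0 | 0.80/0.975 = 0.821 | 7.0% |
| 2.5% | 0.5 | 0.7875/0.975 = 0.808 | 3.6% |

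**4. A concrete case, at c = 0.** With 140 less 20% there are 112 evaluable women. 99/112 just passes (lower limit 0.810). Adding six early stoppers as failures gives 99/118 = 0.839 with lower limit 0.760, which does not pass.

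**5. Power if the decision moves to all treated women.** The rule needs 94/107 or 122/140. The n = 140 column assumes that every enrolled woman is evaluable.

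| All-treated rate | n = 107 | n = 140 |
|---|---|---|
| 0.90 | 0.82 | 0.89 |
| 0.88 | 0.59 | 0.68 |
| 0.855 | 0.30 | 0.34 |

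**The case against.** **PP is a declared target.** The objective begins "The primary objective of the study is to demonstrate the efficacy, as measured by a 4-fold (or more) decrease in rapid plasma reagin (RPR) titer" and goes on to name the 10-day regimen. Sample size considerations places the primary analysis in PP and powers for it. In a Phase II trial, efficacy when the drug is taken is a legitimate question, openly stated. This stands: the choice is not a contradiction within the document. It does not explain why lack-of-effect stoppers are kept as failures while intolerance stoppers are not, or why a PP success should be called efficacious without qualification.

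**The size may be small.** A reader might infer that the PP rate is biased upward in every case, or that the false-declaration risk simply is 18.5%. The documents support neither. The 18.5% needs all 5% to stop before 14 doses and none to be cured. The 5% figure does not say when women stopped, and those who reach 14 capsules can stay in PP. If the excluded women are cured at 80%, there is no inflation.

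**It is not a set of tolerators only.** That reading is also too strong. Women with side effects who reach the threshold stay in, and women who miss doses for other reasons drop out.

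**Intolerance is reported.** Adherence, rescue BPG, discontinuation for intolerance and ITT are all to be shown. This stands, but none of them enters the declaration.

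**The bar's own population is unknown.** The article does not say whether the 80% came from evaluable or all treated patients. If from evaluable patients, an all-treated cefixime rate is not like for like. This stands and should be settled when the set is chosen.

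**The BPG arm.** A reader might add that the two arms' PP rates describe differently selected women. Participant recruitment rules out a direct comparison of the arms, so this adds nothing.

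**Conclusion.** The concern holds in a conditional form. The declaration rests on a set that removes women who stop cefixime early for drug reactions, and no rule brings them back as failures. This favours cefixime to the extent that they are cured less often than the women who remain.

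If 5% leave PP for this reason and the all-treated rate is 0.80, the chance of declaring efficacy at n = 107 lies between 2.3% (no inflation, 80% of them cured) and 18.5% (none cured). If 2.5% leave, it is 3.6% with half cured and 7.0% with none cured. Both the share leaving before 14 doses and their cure rate are assumptions, so the range should be quoted rather than its upper end. The sample-size arithmetic is not in question; what needs attention is the population behind the claim.

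**What to change.** **Preferred.** In Sample size considerations and Primary analysis, base the decision (lower exact 95% limit at least 0.80) on all randomised cefixime women who took at least one dose, whatever their adherence. The Secondary analysis section already uses an at-least-one-dose rule for safety. Use the observed month-6 RPR of women who stopped early. Count as failures those who received BPG before month 6 because of cefixime toxicity, so that a titer fall after BPG is not credited to cefixime. Leave the handling of missed month-6 visits as it is. Keep PP as a supportive analysis.

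**Minimum, if PP stays primary.** Either count women who stop early for cefixime intolerance as failures, as lack-of-effect discontinuers already are, or word a PP-only success as efficacy among women who took at least 14 doses.

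**Cost.** The RPRs are already scheduled and clinical management is untouched, so the edit is to analysis wording. The statistical cost can be more than that. If 90% was meant for adherent women, the cure rate in the deciding set will be somewhat lower and power will fall as shown in step 5: from 0.82 to 0.59 at n = 107 for a rate of 0.88, and to 0.30 for 0.855. The power statement should be redone for whichever set is chosen, saying which women the 90% describes.
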